## **Recruitment (15)**

A list with names and contact details of all individuals aged 59 years or over and registered within the 24 UBSs will be provided by the Health Secretariat of Guarulhos. We will exclude duplicated names and PROACTIVE participants from the list. All individuals in the list will receive a random ID. These IDs will be ordered before entering the study system and the recruitment will follow this order. We will first approach individuals by sending WhatsApp messages to those who have at least one mobile phone number. The message will give a brief introduction to the study and will inform individuals that a research assistant will contact them soon. Initially, only those whose WhatsApp message was successfully delivered will be contacted.

The recruitment comprises three parts: (a) screening; (b) baseline; and (c) invitation to participate in the study. Screening and baseline assessment will be carried out consecutively where individuals will be invited to participate in the study during the same phone call, whenever it is possible. The following are details of each stage of the recruitment process:

**a.** Screening: assessment of inclusion criteria. Before starting the screening, we will inform the participant about the interview and seek consent. Then, we will confirm the age and the use of WhatsApp. Individuals will be screened with the first two questions of the PHQ-9 (PHQ-2). If they present at least one core symptom of depression (depression mood and

anhedonia, i.e. PHQ-2 $\geq$ 1) (28), the evaluation of depressive symptomatology will be completed with the remaining seven questions (11).

**b. Baseline:** Older adults who use WhatsApp, with PHQ-9 $\geq$ 10 (cut-off for depressive symptomatology) (11) and who do not present acute suicidal risk (as assessed by the 9th item of the PHQ-9 and the Immediate Suicide Risk Protocol) or any other exclusion criteria will complete a full baseline assessment.

**c. Invitation to participate in the clinical trial:** after completing the baseline assessment, the research assistant will provide information about the study (type of interventions and follow-up assessments) for all eligible individuals and invite them to participate in the study. Additionally, the WhatsApp number will be 'revalidated' by sending and confirming the receipt of a 'Welcome' message.

## **Assignment of interventions: allocation**

### **Sequence generation (16a)**

Participants will be randomly allocated in a 1:1 ratio to either intervention or control arms. Stratification will be based on the PHQ-9 groups (scores of 10-14, 15-19 and 20+), gender (male and female) and age groups (60-69, 70-79 and 80+ years). Random permuted blocks with random block sizes will be used to generate the randomisation sequence with the support of Microsoft Excel.

### **Concealment mechanism (16b)**

The randomisation sequence will be concealed in the "randomization module" of the Research Electronic Data Capture (REDCap).

### **Implementation (16c)**

The allocation sequence will be generated by members of the research team ([name]) not directly involved in recruiting individual participants, who will be enrolled by an independent research assistant. Data collected will be reviewed by the research coordinator after the participant's consent to participate in the study and the study arm will be allocated with the support of REDCap. The intervention team will receive the list of randomised participants and will send the allocated messages.

## **Assignment of interventions: Blinding**

### **Who will be blinded (17a)**

Given the difference between the number and contents of the messages received by the intervention and control groups, blinding of participants will not be feasible. A list with the participants' allocation group will be sent every week to the researchers responsible for sending the messages. Research assistants will be completely blind to the group allocation during the follow-up assessments and, whenever possible, the research assistant will not carry out more than one assessment (recruitment and follow-ups) with the same participant. The research teams that coordinate the recruitment and intervention will work separately. The assessments and the interventions will be delivered remotely and individually in order to minimise the risk of contamination.

### **Procedure for unblinding if needed (17b)**

No procedure for unblinding is planned for this trial.

## **Data collection and management**

### **Plans for assessment and collection of outcomes (18a)**

Recruitment and the 3- and 5-month follow-up interviews will be carried out by independent research assistants through phone calls. The research assistants will be trained to conduct the assessments and to use the data collection software (REDCap). Quality control of a sample of recorded assessments will be conducted by an independent research assistant. Qualitative assessments will be carried out while participants are receiving the intervention and after the first follow-up assessment.

### *Instruments*

Depressive symptomatology will be assessed using the PHQ-9 (11). This instrument was chosen as it is widely used and there is evidence of validity in Brazil (29, 30). Anxiety symptomatology will be initially screened with the first two questions of the GAD-7 (17) and if GAD-2 $\geq$ 1 (31), the remaining five questions will be assessed. The 3-item UCLA will be used to assess loneliness (18). Quality of Life will be assessed with the EQ-5D-5L (19) and the ICECAP-O (20). Level of depressive symptomatology was associated with these two measures in our previous study (32). Physical and chronic conditions, depression treatment, sociodemographic profile (level of education, personal and household income, marital status, race and living arrangement), alcohol and tobacco use, and use of WhatsApp will also be asked during the recruitment assessment.

During both follow-up assessments, questionnaires completed at baseline will be repeated including the PHQ-9, GAD-7, 3-item UCLA, EQ-5D-5L and ICECAP-O. Participants will also be asked about admissions to hospital and consultations related to mental healthcare and any ongoing treatment for depression. Additionally, questions about the experience receiving the messages will be included for the intervention arm. For every participant, we will request the electronic health record system data on psychotropic medications and consultations with doctors and nurses during the period they were participating in the trial.

### **Plans to promote participant retention and complete follow-up (18b)**

For each follow-up, we will adopt a 4-week window in order to maximise our chances to complete the follow-up assessments. Whenever we have issues with contacting the participant by phone call, we will first send him/her an audio and/or a text message by WhatsApp with a reminder about the assessment. If the participant does not reply to these messages, the UBS manager or an appointed staff member will be contacted to help us reach him/her. If we are unable to find the participant by phone within the first three weeks of the follow-up window, a research assistant will attempt to visit the participant at home to complete a face-to-face assessment.

### **Data management (19)**

All assessment data will be collected and managed using REDCap (33, 34) hosted at the Hospital das Clínicas da Faculdade de Medicina da Universidade de Sao Paulo. REDCap is a secure, web-based software platform designed to support data capture for research studies, providing: 1) an intuitive interface for validated data capture; 2) audit trails for tracking data manipulation and export procedures; 3) automated export procedures for seamless data downloads to common statistical packages; and 4) procedures for data integration and interoperability with external sources.

### **Statistical methods**

#### **Statistical methods for primary and secondary outcomes (20a)**

The analysis for all outcome measures will follow the intention-to-treat principle and adhere to Consolidated Standards of Reporting Trials guidelines for randomised trials (35). To understand if there are any imbalances in risk factors for depression, descriptive statistics will be used to compare differences in baseline characteristics between treatment arms.

All outcomes will be evaluated using regression models that adjust for stratification, the baseline assessment of the corresponding outcome measure. For secondary analyses only, any baseline variables that are not balanced between treatment arms will be accounted for in these models. Logistic regression models will be used to evaluate for the primary outcome (recovery from depression at four months) and the secondary outcome (recovery from depression at eight months). Odds ratios with 95% confidence intervals will be used to estimate recovery from depression at four and eight months. Other secondary outcomes including PHQ-9, GAD-7, 3-item UCLA, EQ-5D-5L and ICECAP-O scores will be assessed using linear regression models. Coefficients and associated 95% confidence intervals for these outcomes represent differences in means between the intervention and control arms. Sensitivity analyses will be conducted to investigate any potential clustering at the USB level.

### Economic analysis

Two economic analyses will be conducted. 1) Incremental cost-effectiveness between the two arms of the trial will be estimated using: a) the primary clinical outcome measure (cost per patient recovered); and b) Quality Adjusted Life Years (QALYs) calculated using the EQ-5D-5L (36, 37). These results will be presented as incremental cost-effectiveness ratios and cost-effectiveness acceptability curves. These show the probability of the intervention being cost-effective at a range of 'willingness-to-pay' threshold levels. 2) The net monetary benefit statistic (NMB), using the difference in costs and the difference in QALYs between the two arms, will be calculated at the WHO recommended threshold for LMICs.

We will conduct the cost-effectiveness analysis from the health system perspective to compare the costs and effects of the 12-week digital psychosocial programme against a single message. The EQ-5D-5L (36, 38, 39) responses will be converted into utility scores using the population tariff most appropriate for the Brazilian population available at the time of the analysis. Utility scores will be used to estimate QALYs, adjusting for baseline values. We will use national, where available, or local unit costs to value resource use.

### Process evaluation

Two assessments of implementation outcomes will be conducted by phone using qualitative interviews. These interviews will provide insight into the reasons, motivations, modes, and contexts of participants from intervention arm that may affect their clinical and

implementation outcomes, as well as the detailed process and content perspectives of how the intervention was received by participants. Approximately 24 participants who received the intervention will be purposively selected for the first assessment, conducted individually, 15 to 30 days after the 3-month follow-up assessment. We will ensure adequate representation from the following subgroups: gender (women and men), age (60-69 years old and 70 years or over), depression status at follow-up 1 (recovered and not recovered from depression). For the second assessment, we will recruit an extra group of 15 individuals using the same inclusion and exclusion criteria of the trial. They will not be included in the main trial analyses so as to eliminate any potential influence these interviews may have on depression outcomes. They will be interviewed weekly by the same research assistant to assess key implementation outcomes throughout the course of the 6-week Viva Vida Programme as well as exploring participants' contextual and behavioural barriers/enablers to the implementation of the intervention. Informed consent to participate and the qualitative assessments will be audio recorded if the participant allows. Interviews will last around 30 minutes.

#### Qualitative analysis

All interviews will be audio-recorded, transcribed and analysis will be conducted using Atlas.TI software. The qualitative assessment applied between follow-up assessments will be thematically analysed deductively using pre-established categories (acceptability, appropriateness, fidelity, and feasibility), as well as inductively for other relevant categories emerging from the analysis. In-depth exploration of participants' experiences will enable us the generation of hypothetical propositions about the relationship between clinical outcomes (considering the PHQ-9 score assessed at the beginning of the study and in the follow-up assessment) and implementation outcomes. Analysis of narratives and images collected during the intervention will also be thematically analysed to understand the user journey (including behavioural activation, contextual barriers, facilitators. etc.) as well as how participants' experiences changed over the six weeks of receiving the intervention.

#### **Methods for additional analyses (e.g. subgroup analyses) (20b)**

A Complier Average Case Effect (CACE) analysis will be used to determine the effect of number of messages listened to on recovery from depression at both four and eight months. A threshold value (listening to most of the messages received) will be used for the CACE

analysis with PHQ-9 scores at both time points. We will use this threshold as it was hypothesised to be the minimum number of sessions needed to have a therapeutic effect. A sensitivity analysis using the thresholds of listening to at least half of the messages or all messages will be conducted, and we will also consider using the number of messages opened to as a continuous variable unless the relevant relationship is far from linear.

Additional exploratory subgroup analyses will be used to estimate whether the following pre-specified characteristics of the participants modified the effect of the intervention: baseline PHQ-9; gender; age; education level; presence of co-morbid physical illnesses. To test for modification, an interaction term will be introduced between the pre-specified variable and the treatment arm. Results of these analyses will need to be interpreted with caution due to the limited power to detect such interactions as well as the paucity of evidence on the theoretical basis for these hypotheses.

#### **Methods in analysis to handle protocol non-adherence and any statistical methods to handle missing data (20c)**

Patterns and the proportion of missing data for the primary and secondary outcomes will be investigated. If there are any marked differences in missing data between treatment arms, or if greater than 10% of the data are missing, multiple imputation using chained equations (MICE models) under the assumption that data is missing at random (MAR) will be used. Data will be imputed separately for the different treatment arms and MICE models will include any variables that predict missingness. Sensitivity analyses testing for modest departures against the MAR assumption will be conducted using the Selection Model Approach.

#### **Composition of the Data Monitoring Committee, its role and reporting structure (21a)**

##### *Data Monitoring Committee (DMC)*

Under the guidance of the TSC, a Data Monitoring Committee (DMC) will be formed comprising an independent Chair, an independent statistician, one other independent member, and at least one of the trial statisticians.

#### **Interim analyses (21b)**

No interim analyses are planned for this trial.

### **Adverse event reporting and harms (22)**

The risk associated with the trial and the digital intervention are considered minimal. Participants will receive any pharmacological and non-pharmacological treatment they were prescribed before or during the study. Also, participants of both arms will receive messages advising them to seek healthcare if the symptoms are not improving or if they are worsening. Identification of acute suicide risk at recruitment or follow-up assessments will activate a standardised protocol, and a family member and the UBS manager will be contacted by the research team. This protocol was successfully applied in the PROACTIVE study (5, 26). Individuals identified with an acute suicide risk during the recruitment assessment will not be eligible to participate in the study.

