##### *Exclusion criteria*

- Individuals with communication issues (non-Portuguese speaking, cognitively impaired or other problem hindering communication to engage in trial assessments or intervention, such as vision or hearing problems)
- Individuals unable to engage in the study for the total period of five months (terminal illness or partner with terminal illness, other)

- Individuals presenting acute suicidal risk (i.e. reported suicidal attempt in the two weeks prior to the screening assessment, as assessed by the 9th item of the PHQ-9 and the Immediate Suicide Risk Protocol)
- Individuals living in the same household as another participant in the study
- Individuals who participated in the PROACTIVE trial

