### **Participant timeline (13)**

Participants will be randomised after granting consent to participate in the trial and will be included in a list to start receiving the messages (both control and intervention arms) no more than 10 days after consenting to participate. Each list will include participants recruited during the previous week who will receive the single message (control group) or the first message (intervention group) on the following Monday. Participants allocated to the intervention arm will receive messages every Monday, Wednesday, Friday and Saturday twice a day during six weeks. The follow-up assessment will occur at three (weeks 12 to 16) and five months (weeks 20 to 24) after receiving the first message. Figure 1 shows the complete timeline of the study.

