### **Sample size (14)**

A sample size of 330-374 individuals will detect a 15 percentage point difference (25% versus 40%) in recovery between the control and intervention groups after three months, with 80-85% power and two-sided 5% significance level. Such a difference in recovery rate is considered clinically meaningful (21-25). We anticipate 25% attrition, which is readily achievable according to the experience we had collecting follow-up data by phone in our previous RCT in Guarulhos, yielding a corrected total sample size of 440-500.

All of the following estimates are based on the PROACTIVE RCT (5) and our pilot study in São Paulo (26). We expect that on average 10% of the individuals registered with each UBS will be aged 60 years or older. On average, there are approximately 1,600 individuals in the eligible age range registered with each UBS. Based on the PROACTIVE data, we would be able to reach 440 individuals by phone and 60% of them (250 individuals) would have a mobile phone and would use WhatsApp application. With a proportion of depressive symptomatology (PHQ-9 $\geq$ 10) of around 20% (26, 27), there would be 50 individuals potentially eligible in each UBS, though this is likely to reduce to 35 once other entry criteria are applied.

We will work with at least 24 UBSs, and we plan to complete recruitment in six months. We will need to screen approximately 25,000 individuals to achieve a sample of 500 participants. Of these 25,000 individuals, we expect that we will be able to contact 6,800. Among the individuals we can contact, 3,800 will use WhatsApp. We expect that at least 20% will have depressive symptomatology (n=760), and 530 will consent to participate in the study – that is, at the upper end of the above range from our sample size calculation.

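### Follow-up checks current suicide risk in both arms, but version 5.0 describes no question on attempts or self-harm since the last assessment and no reporting of attempts, self-harm or deaths as harms by arm

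*Supplement*

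**What the plan says.** All references are to protocol version 5.0 in the Supplement.

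- **Adverse event reporting and harms (22).** Risk is judged minimal, and both arms are advised to seek care if they do not improve. "Identification of acute suicide risk at recruitment or follow-up assessments will activate a standardised protocol", and the family and clinic manager are then told. The section lists no events to be recorded or reported.
- **Instruments (under 18a).** "During both follow-up assessments, questionnaires completed at baseline will be repeated including the PHQ-9". In addition, "Participants will also be asked about admissions to hospital and consultations related to mental healthcare and any ongoing treatment for depression". From records, "For every participant, we will request the electronic health record system data on psychotropic medications and consultations with doctors and nurses".
- **Who will be blinded (17a).** "Research assistants will be completely blind to the group allocation during the follow-up assessments".
- **Data management (19).** All assessment data are held in REDCap.
- **Exclusion criteria (under 10).** Acute suicidal risk is explained as a "reported suicidal attempt in the two weeks prior to the screening assessment", judged from PHQ-9 item 9 and the Immediate Suicide Risk Protocol. The content of that protocol is not shown.
- **Participant timeline (13).** Messages run for six weeks. "The follow-up assessment will occur at three (weeks 12 to 16) and five months (weeks 20 to 24) after receiving the first message".

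**The concern.** A check of current risk answers whether a person is in danger on the day of the call. It does not answer whether anyone attempted suicide or harmed themselves while receiving the programme or after the single message. Everyone enrolled has a PHQ-9 of 10 or more, and one randomisation stratum is 20 and above, so a reader of the results will want that second answer, by arm.

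The programme is automated. Replies from participants get an automated response only. Staff calls in the first two weeks concern problems receiving or opening messages (11c). For main-trial participants, the follow-up interview is therefore the first planned occasion on which staff would ask about events during the programme. If the question is not asked then, an event that never reached a health service leaves nothing to find later. The statement that risk is minimal would remain an expectation that the trial had not tested.

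**Working it through.** The plan states no figure on this point to reproduce. The check is a comparison of sections plus simple timing.

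**1. What each source could reveal about an attempt between assessments**

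| Source (version 5.0) | Both arms? | What it could show | What is not described |
|---|---|---|---|
| PHQ-9 at both follow-ups (Instruments) | Yes | Item 9, as part of the current risk check | Attempts or self-harm since the last assessment |
| Acute-risk response (22) | No arm restriction stated | People at acute risk when assessed | Recording the finding as a harm |
| Questions on admissions, mental-health consultations, depression treatment (Instruments) | Yes | Attempts that led to care, indirectly | That the cause was an attempt |
| Health records: psychotropics and consultations (Instruments) | Yes | Care contacts, indirectly | Attempts, self-harm or deaths as such |
| Contact efforts through the clinic manager or a home visit (18b) | Yes | A death might come to light | Recording it as a harm |
| WhatsApp replies (11a, programme replies) and qualitative interviews (Process evaluation) | Intervention recipients only, as described | Chance disclosures | Any use for harms |

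**2. Whether another section fills the gap.** The outcomes (12) include no harm. The statistical sections (20a to 20c) contain no safety summary. The Data Monitoring Committee section (21a) gives membership only. Section 23 gives the steering committee a report on trial conduct, with no safety content stated.

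**3. Timing.** Inputs from Participant timeline (13): programme weeks 1 to 6; first follow-up in weeks 12 to 16; second in weeks 20 to 24; messages start at most 10 days after consent.

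- From programme end to first follow-up: 12 − 6 = 6 weeks, up to 16 − 6 = 10 weeks.
- Look-back needed at the first follow-up to reach the first message: 12 to 16 weeks, and up to 10 days more to reach consent.
- Between the two follow-ups: 20 − 16 = 4 weeks, up to 24 − 12 = 12 weeks.

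A question worded as since the last assessment covers these intervals whatever their length. A question about the present, or about less than the preceding 6 weeks, reaches none of the programme even at the earliest first follow-up.

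**4. What is left uncovered.** Attempts that led to an admission, consultation or prescription may be partly recoverable, equally by arm. Attempts with no such contact are not, unless the risk protocol asks everyone about the whole interval.

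**The case against.** The strongest objection is that the Immediate Suicide Risk Protocol is not shown. It may already ask about the whole interval, and the list of repeated questionnaires is worded as inclusive, not closed. This stands: the documents show that a question is not described, not that it is not asked. It does not reach the second half of the point, because reporting of attempts, self-harm and deaths would still be undescribed. No separate SAP is shown, and the layout of a safety table could be left to one. Which events are sought and counted as harms belongs in the protocol's harms section.

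The context also counts for the plan. People at acute risk are excluded, both arms are advised to seek care, the intervention is a series of messages, and a monitoring committee with independent members is planned. That limits the severity but does not supply the missing information.

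Three stronger readings are tempting, and the documents do not support them.

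- *A reader might infer that suicide-related answers go unrecorded.* Data management (19) puts all assessment data in REDCap, which would include item 9. What is missing is the question about the interval, and the classification and reporting of events.
- *A reader might carry the two-week window to follow-up and conclude that only a small, fixed share of follow-up time is covered.* The window is an eligibility rule tied to screening, and no section applies it later. Coverage percentages built on it, or on any other assumed window, would describe the assumption and not the plan.
- *A reader might take "We anticipate 25% attrition" to mean that a quarter of participants are never interviewed.* Sample size (14) attaches that figure to a calculation for recovery at three months. Someone missed then can still be interviewed at five months, and section 18b adds reminders, clinic contact and a home visit. The number with no interview at all is not given.

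**Conclusion.** The point holds as a gap in what the protocol describes. Version 5.0 gives both arms the same check of current suicide risk but describes no question on attempts or self-harm since the previous assessment, and no classification or by-arm reporting of attempts, self-harm or deaths as harms.

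The consequence is conditional. If the unseen risk protocol does not ask everyone about the whole interval, an attempt during the six-week programme that led to no admission, consultation or prescription would not be identified. If it does ask, the gap in the question is nil and only the recording and reporting remain to be stated.

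The number of events at stake cannot be given, since the plan states no attempt rate. The primary outcome, its estimate and its analysis are untouched. The change is worth making but is not critical to the trial's main result. Confidence is medium because of the document that is not shown.

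**What to change.** **Instruments (under 18a).** At both blinded follow-ups, ask every participant in both arms, in the same words, about any suicide attempt or self-harm since the previous assessment (since baseline at the first follow-up), with an approximate date. Someone missed at the first follow-up should be asked at the second about the whole period since baseline. If the risk protocol already contains this question, ask it of everyone and record the answer.

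**Adverse event reporting and harms (22).** State that attempts, self-harm and deaths are reported descriptively by arm, with the number assessed in each arm. Include deaths learned of through contact attempts or the clinic manager (18b). State that disclosures through channels described only for people receiving the intervention, namely WhatsApp replies to the programme and the qualitative interviews, are listed separately. Counting them in the comparison would make ascertainment unequal.

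**Cost.** One or two questions in two existing interviews, a few REDCap fields and an ethics amendment, with no extra visits or staff. The downside is a slightly longer call with a sensitive question and possibly more activations of the risk protocol.
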